#### Error and Failure Rates

Critical errors occur when participants make operational errors during interaction with the machine-guided tool. Project staff will aid participants, if needed, to ensure accurate completion of all behavioral questions that contribute directly to risk assessment scores.

The failure rate (cases where the risk score is high and the test result remains negative for both visits) will be identified and reported as the number or a percentage of failed cases of the total number of cases completed in the study.

It should be noted that failure due to critical errors (participants not being able to successfully complete the digital assessment) will not be included in the analysis.

The type of behavioral questions and the weighted score for each will be monitored and evaluated for continuous improvement and refinement purposes.

#### Missing Data

The study will use electronic data capture for each participant, which requires that each question be completed before moving on to the next. This will eliminate the possibility of missing data during the data collection section of the study. Any participant record with missing results for a HIV test will be removed from the study.

#### Sensitivity Analysis

The performance of the model will be analyzed using the validation data set from the data split using a confusion matrix (Figure 5) that will allow for the calculation of sensitivity, specificity, and accuracy.

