**Methods:**

In total, 200 HIV-negative adult individuals across three South African study sites each (two semirural and one urban) will be recruited. Study processes will include (1) completing a series of questions (demographic, sexual behavior and history, personal, lifestyle, and symptoms) on an application system, unaided (assistance will only be provided upon user request); (2) two HIV tests (one per study visit) being performed by a nurse/counselor according to South African national guidelines (to evaluate the prediction accuracy of the tool); and (3) communicating test results and completing a user experience survey questionnaire. The output metrics for this study will be computed by using the participants’ risk assessment scores as “predictions” and the test results as the “ground truth.” Analyses will be completed after visit 1 and then again after visit 2. All risk assessment scores will be used to calculate the reliability of the machine-guided tool.

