### Design

In this longitudinal, supervised learning study, the data collected will be split into a training set and a validation set and the data used to validate the model will not be used in the training of the model, which will eliminate the need for a control group. This study will build on the feasibility study described before. The major variable shift is from a clinic-based setting to an in-field setting, which includes rural and semirural sites.

During the evaluation, the untrained user will be assessed thoroughly for process success or difficulty by a silent, non-interacting nurse/counselor. Overall, the process will include (1) completing a series of behavioral questions on an application system without the assistance of trained staff (assistance will only be provided on user request); (2) HIV testing being performed by the trained nurse/counselor (for comparator data to the risk assessment scores); and (3) communicating test results and completing a survey questionnaire developed to collect data on user experience.

All participants will have two rapid HIV tests performed. In the event of a positive HIV diagnosis, the participant will be referred for clinical treatment and care. If a participant tests negative, they will be found eligible for visit 2, which will occur 3 months after visit 1. At visit 2, the participant will follow the same process as that completed at visit 1 (Figure 2).

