### Blinding of Results

This will be a blinded study. Participants will not be aware of their risk assessment scores. There will be no randomization of participants, as all participants will be required to interact with the machine-guided tool. This study will make use of supervised learning in which the data set will be collected and then used to train and test the machine learning model that has been created. The data will be collected in a specific area, and selection will be random. The data, however, will be split into training and validation data using a randomized split algorithm commonly found in statistical and data processing languages such as R and Python.

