#### Machine Learning Algorithm

The first phase of this machine-guided diagnostic study will be used to compare potential supervised learning algorithms to determine which algorithm is the most robust in variable variation. The algorithms that will be compared are K-nearest neighbor, logistic regression, neural network, random forest, support vector machine, and XGBoost. These models will be compared using a confusion matrix by comparing sensitivity, specificity, accuracy, precision, and negative predictive value. When comparing models, the relative risk of a false negative versus a false positive will be taken into consideration to minimize the risk of potentially high-risk patients not being flagged for further screening.

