#### Interaction Between Variables

A bivariate analysis will be performed for each variable to investigate the relationship between the respective variable and HIV status. This will then further be used in feature engineering.

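### The plan keeps validation data out of model fitting but secures no performance estimate free of algorithm and feature selection, so reported accuracy may be optimistic

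*Protocol article*

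**What the plan says.** All references are to the protocol article.

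- **Design** names two sets and promises that "the data used to validate the model will not be used in the training of the model".
- **Blinding of Results** repeats the two-way division: the data are "split into training and validation data using a randomized split algorithm". The split fraction is not given.
- **Machine Learning Algorithm** lists six candidates. "These models will be compared using a confusion matrix", on sensitivity, specificity, accuracy, precision and negative predictive value, with weight given to the relative risk of false negatives. The data set for this comparison is not named.
- **Sensitivity Analysis** says "The performance of the model will be analyzed using the validation data set from the data split", again by confusion matrix. It is the only place that says which data a confusion matrix will use.
- **Interaction Between Variables** says "A bivariate analysis will be performed for each variable to investigate the relationship between the respective variable and HIV status", and that the result goes on into feature engineering. No restriction to training data is stated.
- **Abstract, Methods** says "All risk assessment scores will be used to calculate the reliability of the machine-guided tool".

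**The concern.** A performance figure is unbiased for a chosen model only if the data behind it played no part in choosing the model. Keeping validation records out of the fitting step is necessary but not sufficient. If those records also decide which of six algorithms wins, or which variables are engineered into features, the reported figures are partly selected for being high.

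The Design section protects fitting only. With two named sets and one named source for the confusion matrix, nothing in the article reserves data for a final estimate. The Abstract's use of all scores adds a second route: if those scores come from the model trained in this study, the calculation includes people the model was fitted to.

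The Results section makes the tool's accuracy a main deliverable. Optimistic sensitivity would hide the missed high-risk people whom the Machine Learning Algorithm subsection wants to protect. The Skewed Data subsection expects a lowered HIV prevalence, so validation positives may be few, and selection optimism grows as they become fewer.

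**Working it through.** **The plan's own figure.** 3 sites × 200 = 600, as stated under Sample Size. The article gives no split fraction, prevalence or target accuracy, so the rest is sized under assumptions.

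**Inputs.** From the article: 600 participants and six algorithms. Assumed: a 30% validation share; prevalence 5%, 10% or 15%; true sensitivity and specificity of 0.70 for all six algorithms; correlation ρ between algorithms from 0 to 0.9.

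**Validation records.** 600 × 0.30 = 180. Positives: 180 × 0.05 = 9; 180 × 0.10 = 18; 180 × 0.15 = 27.

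**Exact check at ρ = 0 with 9 positives.** With F the Binomial(9, 0.70) distribution function, the expected best of six is (1/9) × Σ over k = 0 to 8 of [1 − F(k)⁶]. The terms that matter are F(8) = 0.960, F(7) = 0.804 and F(6) = 0.537, whose sixth powers are 0.781, 0.270 and 0.024. The sum of all the sixth powers is about 1.075, so the result is (9 − 1.075)/9 = 0.88, against a true 0.70.

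**Correlated algorithms, by simulation.** Algorithm a is correct for person i when √ρ·cᵢ + √(1−ρ)·eᵢₐ < Φ⁻¹(0.70), with c and e standard normal. There were 8,000 runs per row, with ties broken at random. The entries are the mean apparent sensitivity of the winner.

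| Positives of 180 | ρ | Chosen on sensitivity | Chosen on Youden (sens + spec − 1) | Chosen on accuracy |
|---|---|---|---|---|
| 9 | 0 | 0.88 | 0.88 | 0.75 |
| 9 | 0.7 | 0.83 | 0.83 | 0.73 |
| 9 | 0.9 | 0.79 | 0.79 | 0.72 |
| 18 | 0 | 0.83 | 0.83 | 0.74 |
| 18 | 0.7 | 0.79 | 0.79 | 0.73 |
| 27 | 0 | 0.81 | 0.80 | 0.74 |
| 27 | 0.7 | 0.78 | 0.77 | 0.73 |
| 27 | 0.9 | 0.76 | 0.75 | 0.72 |

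The optimism is therefore 0.05 to 0.18 if the winner is chosen on sensitivity or Youden, and 0.02 to 0.05 if chosen on accuracy. It is upward in every row. Data not used for the choice would return 0.70 on average.

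**Precision.** At 5% prevalence the whole sample has 600 × 0.05 = 30 positives, of which the split leaves 9 for evaluation. Clopper-Pearson 95% intervals: 7/9 gives 0.40 to 0.97; 24/30 gives 0.61 to 0.92. Resampling that gives every participant an out-of-fold score uses all 30. The second interval is only a guide to the gain, because cross-validated scores are not fully independent.

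**The case against.** The strongest reply is that much of this is silence in a condensed article. The Design section expressly separates validation data from training, and performance is reported on the validation set. The Machine Learning Algorithm subsection does not say that the six are compared on that set, so comparison by resampling within the training data is not excluded. The bivariate analysis is not said to use all records. Reliability in the Abstract is undefined and could refer to scores from a tool that already exists. The full protocol or the SAP, neither of which is shown, may settle these points. The size also depends heavily on the selection rule: a winner chosen on accuracy shows little optimism in sensitivity.

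Most of this stands as a limit on the claim. It rules out saying that validation is simply not independent, or that performance will be overstated. It does not remove the point. The article fixes a two-way split and names the validation set as the source of reported performance, and it leaves no data protected from selection. The Abstract's wording needs reconciling with the Design section whatever an SAP says.

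Three further inferences should not be drawn:

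- **That the visit 2 comparison re-tests the people whose visit 1 results trained the model.** The Skewed Data subsection places both visits in the second phase and does not say whether phase 1 is the earlier feasibility study. The documents do not establish an overlap.
- **That the bias can be stated as an inflated AUC.** The article's metrics come from a confusion matrix. Any AUC figure would also need an invented number of uninformative items and an invented screening rule.
- **That leaving one site out would test the move from clinic to field.** All three sites are in-field, so it would test transfer between sites.

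**Conclusion.** The point holds in a limited form. Validation records are kept out of fitting, but the plan secures no estimate that is free of algorithm and feature selection, and the Abstract's use of all scores conflicts with the Design section if those scores come from the model trained here. Reported performance may be optimistic. With 9 to 27 validation positives and a true sensitivity of 0.70, the winner of six would show about 0.75 to 0.88 if chosen on sensitivity or Youden, and 0.72 to 0.75 if chosen on accuracy. Prevalence, split fraction, equal true accuracy and correlation are assumptions. The figures also suppose that the set that picks the winner supplies its results, which is the likely reading but is not stated. The possible effects of feature engineering on all records and of scoring training participants are not included in these figures.

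**What to change.** 1. State that bivariate analysis for feature engineering, the feature engineering itself, the choice among the six algorithms and the choice of risk cut-off use training data only (inner folds).
2. Report performance only on data used for none of these steps. Repeated stratified nested cross-validation is preferable, with both visits of a person in the same fold, because it also lets every positive contribute to the evaluation. A separate held-out test set would also be valid, but would leave few positives.
3. Limit the Abstract's reliability calculation to out-of-fold or held-out scores, and say what reliability means. If the scores come from a tool built before this study, say so.

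The cost is more computing, some added wording and probably somewhat less favourable reported performance. No new data are needed. The change should be in place before the analysis that follows visit 1.

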**Figure 5 figure5:**
[figure not shown]
Confusion matrix with classification metrics [14].

#### Interaction Between Variables

A bivariate analysis will be performed for each variable to investigate the relationship between the respective variable and HIV status. This will then further be used in feature engineering.

#### Post Hoc Analysis

In machine learning, post hoc analysis is not commonly performed, and a comparison of model performance through the analysis of a confusion matrix and confidence curves offers an alternative to conventional omnibus tests [15].

#### Skewed Data

The participants enrolled in this study who are either HIV negative or of unknown HIV status will cause a lower HIV prevalence in the sample data set. However, this will be done so as to remove the possibility of participants who are HIV positive creating a bias in the supervised learning, as these people may have altered behavior due to being HIV positive, which may result in risk reduction behavior, reducing the sensitivity and accuracy of the model. The skewed data set will be accounted for in the second phase of the study, where participants will perform two visits, including a follow-up HIV test, which will allow for the analysis of a comparison to the predictive ability of the machine learning model created in phase 1.

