## Introduction

A recent study by Nguyen et al [1] showed that albeit the current progress achieved by some African countries in the effort to work toward reaching the Joint United Nations Programme on HIV/AIDS (UNAIDS) targets of human immunodeficiency virus (HIV) testing, the prediction shows little chance in achieving this by 2030. None of the African countries analyzed shows a high probability of achieving the targets; however, only three countries still have a chance of attaining this, with a probability below 50%. This may suggest that countries heavily affected by HIV may require substantial efforts, such as increased support from global organizations, to make progress toward the UNAIDS targets. Additionally, there is a need to find and make more effective changes in the previous strategies for encouraging behavioral interventions to increase condom usage, and strengthen HIV programs in many of the most affected countries. HIV-screening programs therefore are largely invested in preventing HIV transmission by promoting regular testing and continuous development of innovative prevention methods and messages [2,3]. Mobile technology has played a role in advancing health programs [4,5], and studies have shown that an automated risk prediction model can successfully be used to identify patients who exhibit a high probable risk of contracting HIV [6-8]. One of these studies demonstrates that with the use of machine-guided risk assessments, the process of pre-exposure prophylaxis (PrEP) initiation can become more efficient and suitable.

Although identifying persons who are at high risk of contracting HIV should enable a more targeted and cost-effective approach for prevention programs, universal screening programs are costly and labor intensive and do not have as high a success rate in identifying high***-***risk individuals [6,9].

Supervised learning is used to train machine learning models by using patient traits as inputs. There are two broad categories of patient traits:

Generic patient traits, such as age, gender, disease history, and moreDisease-specific traits, such as sexual behavior in the context of HIV

In the supervised learning paradigm, we need to know the ground truth to train the model, which in this case is a medical outcome, such as a diagnostic test result. The relationship between patient traits and outcomes can be analyzed by measuring the performance of the model [10,11].

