### Study Population

This is a general population study of adult males and females who are self-reported HIV negative or have an unknown HIV status in order to assess the capability, from device interaction, of identifying those who are potentially at high risk for contracting HIV. Recruitment will take place in different geographical regions using multiple recruitment methods, increasing the chances of the study population being representative of the general population.

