### Enrollment Questionnaire: Inclusion/Exclusion Checklist

An enrollment questionnaire will be administered to establish successful qualification for enrollment. The questionnaire will clearly outline the inclusion and exclusion criteria. If participants satisfy all the inclusion criteria and none of the exclusion criteria, eligibility for enrollment will be confirmed. Enrollment questionnaires will be available in English and will capture information such as participant identification, name and surname, date of birth, nationality, employment status, and recruitment site. Information such as participant initials, date of birth, gender, date of enrollment, and reason for exclusion will be captured on an enrollment log. Once a participant has qualified for enrollment and has signed the informed consent form, the participant will be assigned a unique identification number. Volunteers who do not satisfy inclusion criteria will be documented and reported as exclusions. Further, the reason for enrollment failure will also be recorded.

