### Demographic and Health Data Collection

All enrolled participants will have the following demographic data captured:

InitialsDate of birthAgeGenderNationality

The participant background information captured will include:

Employment status (employed/unemployed)Years of schooling and level (≤grade 7 primary schooling level/≥grade 8 primary schooling to ≤matric level/≥Technikon, university, and university plus)Reading/writing impairmentLanguage preferenceHIV status (if known)Approximate date of last HIV test

Participants may choose to report their medical health history, which will be documented and archived for statistical review. Information will include:

Self-reported HIV status:Unknown status/never been testedNegative statusSelf-reported medical conditions:DiabetesHypertensionVisual impairmentPregnancyOther

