**Figure 4 figure4:**
[figure not shown]
Number of partners and age groups selection box.

A trained nurse/counselor will proceed to perform two rapid HIV tests and communicate the results to the participant. If the results are HIV positive, the participant will be counseled and encouraged to commence antiretroviral therapy at a clinic of their choice. If the results are HIV negative, the participant will be eligible for visit 2 (3 months after visit 1) and will be issued with an appointment card. If the results are discordant, the nurse/counselor will be required to repeat testing. Additionally, the participant will be sent visit 2 appointment reminders through text messages monthly.

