#### Confirmatory Procedures

HIV status will be confirmed using the rapid diagnostic kits in-use (First Response HIV 1-2-0 and Alere DetermineHIV-1/2) at the testing site. If the confirmatory rapid test is HIV positive, the participant will be referred to a clinic of their choice for treatment and care.

In the event the second rapid test shows a negative result, the HIV status will be considered indeterminate, and all tests will be repeated (Textbox 1) [13].

Interpreting test results. RDT: rapid diagnosis test.RDT1 (positive) + RDT2 (positive) = positiveRDT1 (negative) + RDT2 (negative) = negativeRDT1 (negative) + RDT2 (positive) = indeterminate (repeat test)RDT1 (positive) + RDT2 (negative) = indeterminate (repeat test)

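### The eligibility rule can reduce, but not remove, bias from people already diagnosed with HIV, because entry status is self-reported and no described step after a positive visit-1 result identifies an earlier diagnosis

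*Protocol article*

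**What the plan says.** The Skewed Data section concedes that the entry rule will lower HIV prevalence in the sample and gives the reason for accepting this: "this will be done so as to remove the possibility of participants who are HIV positive creating a bias in the supervised learning". It names the mechanism by which the model would suffer: "these people may have altered behavior due to being HIV positive, which may result in risk reduction behavior, reducing the sensitivity and accuracy of the" [...].

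The rule works through what the volunteer says. Study Population describes "adult males and females who are self-reported HIV negative or have an unknown HIV status". Exclusion Criteria rule out people with a known positive status and people currently on PrEP or HIV treatment; identification documents are required for age only. The Enrollment Questionnaire section states "An enrollment questionnaire will be administered to establish successful qualification for enrollment". Demographic and Health Data Collection records known status and the rough date of the last test, and adds: "Participants may choose to report their medical health history, which will be documented and archived for statistical review". The tablet questions ask how long ago the last test was.

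For the reference result, Confirmatory Procedures state "HIV status will be confirmed using the rapid diagnostic kits in-use", and the result table has three outcomes: positive, negative and indeterminate. On a positive result, Testing Procedures say: "If the results are HIV positive, the participant will be counseled and encouraged to commence antiretroviral therapy at a clinic of their choice". The Introduction makes the test result the training label: "we need to know the ground truth to train the model, which in this case is a medical outcome, such as a diagnostic test result". Design and Blinding of Results then split the collected data at random into training and validation sets.

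**The concern.** The reason given for accepting fewer positives is that a specific bias is taken away. The design described can only make that bias less likely. A person who withholds a known diagnosis at entry looks the same in the data as a person diagnosed for the first time at visit 1.

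Visit-1 positives will be few, because known positives are screened out, and any undisclosed known positives fall within that small group. They would affect both model fitting and the confusion matrix used to choose among six algorithms. The error they would tend to produce, a positive person scored as low risk, is the one that the Machine Learning Algorithm section says it wants to keep down. As described, the data could not show afterwards whether the problem was negligible.

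**Working it through.** **Tracing one undisclosed known positive through the plan**

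1. *Entry.* Status is self-reported and applied through the enrollment questionnaire. No record check or treatment check is described. The self-reported status options listed are unknown/never tested and negative, so a person who conceals a diagnosis falls into one of these.
2. *Tool.* The behavioral questions look back over recent periods (partners in 3 months, sexual activities in 6 months). For someone diagnosed before those periods, the answers describe behavior after diagnosis, which is what the Skewed Data section is worried about.
3. *Testing.* Two positive rapid tests give a positive result. The result table has no category for an earlier diagnosis.
4. *After the result.* Counselling and referral are described. A question on earlier diagnosis is not.
5. *Data set.* The label is positive and the record enters the random split. Under Missing Data, the only removal tied to HIV testing is for a missing result.
6. *Visit 2.* Only visit-1 negatives continue. This person leaves follow-up, but the visit-1 label stays in the phase 1 data.

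**Size: illustration only**

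The one relevant figure in the article is the sample size: 3 sites × 200 = 600, which reproduces. Prevalence, non-disclosure rate, split ratio and tool sensitivity are not given, so all values below are assumptions.

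*Share of positives affected.* Let m be the fraction of enrolled people who are undisclosed known positives and d the fraction who are undiagnosed positives. The share among visit-1 positives is k = m / (m + d).

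| Assumed m | Assumed d | People (of 600) | k |
|---|---|---|---|
| 0.5% | 5% | 3 and 30 | 3/33 = 9% |
| 0.5% | 2% | 3 and 12 | 3/15 = 20% |
| 2% | 5% | 12 and 30 | 12/42 = 29% |
| 2% | 2% | 12 and 12 | 12/24 = 50% |

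*Effect on apparent sensitivity.* Apparent sensitivity = (1 − k) × Se(undiagnosed) + k × Se(known).

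- With 0.80 and 0.50, this is 0.80 − 0.30k: 77% at k = 10%, 74% at 20%, 68% at 40%.
- With 0.80 and 0.40, this is 0.80 − 0.40k: 76% at k = 10%, 70% at 25%, 60% at 50%.
- If the tool did equally well in both groups, this formula would give no change at any k.

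*Validation set.* The table gives 15 to 42 positives in total. With an assumed 30% validation share, that is 15 × 0.3 = 4.5 to 42 × 0.3 = 12.6 positives. At that size, a few such people are enough to move the estimate.

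**The case against.** The strongest reply is that the sentence states a purpose. It explains why known positives are excluded, the article says openly that status is self-reported, and the mechanism is hedged with the word may. Reliance on self-report is common to studies of this kind. This stands in part: the sentence should not be read as a guarantee of error-free screening. It is still the plan's reason for accepting fewer positives, and the benefit it names is larger than the design can deliver.

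A reader might infer that the plan never asks about earlier diagnosis. The documents do not support that. The enrollment questionnaire covers the exclusion criteria, known status and last test date are recorded at entry, and the tablet asks about time since the last test. The gap is narrower: all of these are entry self-reports, and no described step revisits the matter after a positive result.

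A reader might also infer that the contamination is large. Nothing in the article gives a non-disclosure rate or suggests that it is material.

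The plan already has routes for ineligible participants: the investigator may withdraw them, and enrollment against the criteria is a protocol violation. Those routes act only on ineligibility that has been detected.

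Counselling content may sit in operating procedures that are not shown, and an extra sensitivity analysis may sit in an analysis plan. That is fair, and the point therefore rests on what the article claims for its eligibility rule. Finally, a post-test question relies on self-report again, so it will not catch everyone.

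**Conclusion.** The point holds in a limited form. The eligibility rule reduces the chance of bias from already-diagnosed people; it does not remove it. Any who are undisclosed at visit 1 would be labelled as true cases in the training and validation data and, by the plan's own reasoning, may lower sensitivity and accuracy. The amount cannot be estimated from the documents. The illustrative sensitivities of 60% to 77%, against an assumed 80%, depend wholly on assumed inputs, and the true effect could be close to nil.

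That the rapid tests do not separate new from earlier-diagnosed infection is inferred from the three result categories; the article does not say so in words.

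It would be wrong to extend the point to the visit-2 analysis. Changes from nonreactive to reactive are largely protected, because people labelled positive at visit 1 do not continue. The phase 1 model, which is then compared with the follow-up results, is still built on the uncleaned visit-1 labels. This is an inexpensive improvement worth making, and the study does not fail without it.

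**What to change.** 1. In Skewed Data, say that the eligibility rule reduces this bias, and acknowledge that it depends on self-report.
2. After a positive visit-1 result, record one neutrally worded data item on any earlier positive HIV test or any HIV treatment.
3. For the analysis, treat those who say yes as not meeting the existing Exclusion Criteria, so that the main training and validation set is free of identified known positives.
4. Report sensitivity and accuracy with and without them, and give their number.

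The cost is one item for the few visit-1 positives and one additional analysis. The testing, counselling and referral steps stay as written. There are two downsides: some non-disclosure will remain, and the main analysis set loses a few positives from a group that is already small.
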